**Unit Based Mentoring Protocols**			

**Structured Mentoring (by Research Facilitator)** During the 2 weeks following each in-class session, the researcher engages each participant in a 10-min session to discuss and reflect on his/her experiences applying CONNECT concepts. The researcher uses a semi-structured guide to elicit concerns about using the strategies.	Facilitates authentic learning, which occurs only when learners can directly and independently apply concepts [75].	All CONNECT participants	2, 10 min sessions (20 min total)

**Chance Encounter Mentoring (by In-house Facilitator)** In-house facilitators engage in point-of-care discussions with staff to practice CONNECT behaviors and jointly problem solve, using the 'chance encounter' protocol. They record the number and descriptions of chance encounter mentoring sessions. At least 5 such encounters should occur daily during naturally occurring usual work activities.	Identifies staff concerns and barriers, facilitates ongoing learning about interaction, and strengthens sustainability of new behaviors. Facilitators learn to use existing time differently.	In-house Facilitators engage with floor staff in their department or work unit	1.25 hrs/day for in-house facilitator (37 hrs total)

**Table 2 T2:** FALLS protocol activities, rationale, who is involved and time required

FALLS Protocols	Rationale/Outcome	Who	Time
FALLS Coordinator and Team Role			

Training Session Researcher reviews: 1) role of FALLS Coordinator and Team members; 2) Falls Management Program rationale and main components; 3) annotated slide presentation on practical aspects of fall prevention; 4) toolkit materials; 5) study expectations.	Falls Team members champion fall prevention, identify area to improve, monitor changes.	FALLS Coordinator, Falls Team, DON	1, 4 hrs session

Weekly FALLS Team teleconference Researcher contacts FALLS team weekly during 3-month intervention for problem-solving/discussion, and highlights a topic from the Fall Management Program in more depth. Topics include 1) staff fall prevention education; 2) medications and falls 3) patient and family fall education; 4) orthostatic hypotension; 5) vision assessment and intervention; 6) gait and balance assessment and intervention 7) environmental assessment and intervention; 8)challenging behavior management; 9) establishing a culture of safety; 10) audit and feedback; and 11) Wrap-up and re-setting goals	Reinforces key concepts of multi-factorial risk reduction, supports FALLS Coordinator and maintains enthusiasm.	FALLS Coordinator, and any other team members s/he wishes	11, 30 min sessions weekly (5.5 hrs total)

Staff Education			

Case-Based Modules (online and paper form) Nurse module. Covers impact, fall risk factor assessment and intervention focusing on orthostatics, gait, toileting, medications, environmental hazards. NA module. Covers fall risk factor identification and intervention focusing on gait, footwear, toileting, hip protectors, and environmental hazards. Prescriber/pharmacist module. Covers epidemiology/impact, risk factor assessment, risk factor reduction focusing on psychotropic medication reduction and Vitamin D.	Uses case-based learning to impart knowledge and change attitudes about multi-factorial fall risk reduction.	RNs, LPNs, NAs, MDs, NPs, PAs, Consultant Pharmacists and others (PT, SW, Activities etc)	30-60 min

Post-Fall Problem-solving			

Academic Detailing Nursing home frontline staff is invited to participate in consultations with the researcher and FALLS Coordinator regarding their most challenging residents with falls, modeling risk factor assessment and multi-factorial interventions. Sessions occur at each nursing station during the day and evening shifts.	Reinforces key concepts and promotes behavior change and interdisciplinary discussions [75].	Nurses, NAs, other interested staff	2, 20 min sessions (40 min total)

Audit and Feedback			

Feedback Report Report uses visual (bar graph) and written depictions of the nursing home's current practice on fall-related process and outcome measures, and how this compares with peer nursing homes. Researcher presents and explains the feedback report to FALLS Team.	Identifies areas for improvement, promotes behavior change [75].	FALLS team, others as desired by Falls Coordinator	30 min

Toolbox			

Morse Fall Scale: Validated scale that quantifies fall risk in nursing home residents; Nurse Fall Risk Reduction Worksheet: Prompts nurse to identify and modify reversible fall risk factors. Can be used for chart documentation; Prescriber/Pharmacist Medication Reduction Worksheet: Prompts consideration of dose reduction or discontinuation of high fall-risk medications, including lower risk substitution options; Environmental Checklist: Facilitates identification of hazards in resident room, bathroom, and common areas; Wheelchair maintenance log and stickers: Facilitates regular assessment and repair of wheelchair brakes; Fall Risk Fax Communication Form: Allows nurse/pharmacist to communicate concerns about medications with prescribers; Patient and Family Brochure: Describes interventions that the nursing home is using to reduce falls; Physician/Prescriber Brochure: Describes the fall reduction program and encourages review of medication reduction worksheets and faxes.	Provides modifiable tools to assist with communication, implementation, and documentation of multi-factorial risk reduction.	FALLS Coordinator determines dissemination	Voluntary

### Treatment fidelity

Our treatment fidelity protocols use the National Institutes of Health Behavior Change Consortium's [76] model of treatment fidelity.

### Design

To ensure design fidelity, we standardized the CONNECT and FALLS protocols to a specified dose in terms of number, frequency, and length of contact.

### Training

CONNECT and FALLS will be delivered by different research interventionists trained separately to minimize contamination. The protocol specifies training content, structured practice, and role-play exercises to ensure that interventionists' skills meet established standards.

### Delivery

To ensure that CONNECT and FALLS are delivered as intended, a research team member will observe the interventionists on a random schedule, completing standardized checklists. The interventionists and PIs will discuss the results and problem-solve barriers to adherence and repeat concepts and role-play as needed. We will track participants that complete study components. For CONNECT, we will use: contact summary sheets for each visit to a research site; databases for interventionists to record contacts with participants; and sign-in sheets to document participation in sessions. For FALLS, we will use: contact sheets to record each contact between interventionists and the Fall Team; sign-in sheets to document participation in post-fall problem-solving sessions; and databases to track completion of educational modules via requests for continuing education credit or certificate of completion.

### Receipt of treatment

For CONNECT, participants' self-monitoring of local interactions will provide a measure of adherence and behavior change. The class sessions will include discussion and practice during which skills can be systematically assessed. For FALLS, participants will complete post-tests in the educational modules.

### Enactment of skills

Researchers will systematically assess enactment when they shadow the in-house facilitators to observe how they practice mentoring behaviors. The researchers will also assess and record enactment by participants during structured mentoring. Finally, they will assess enactment by observing at least two orientation sessions in which the in-house facilitator delivers the in-class session to new employees. Fall risk reduction indictors will be used to measure enactment of the FALLS intervention.

### Recruitment and data collection procedures

#### Staff recruitment and consent

When we recruit nursing homes, administrators and directors of nursing will agree to include CONNECT & Learn sessions and/or FALLS modules as regular in-service training. In meetings (e.g., nurses meetings, CNA meetings), researchers will explain the study and invite staff to participate in the other aspects of the study (completing surveys, structured mentoring). Staff not attending meetings will be approached individually. A research team member will answer questions and obtain written informed consent.

#### Staff incentives

As in our prior studies, we will offer an exit-interview consultation [77] during which we will share study results with participants. Continuing education credits or a certificate of completion will be given to staff for completing CONNECT & Learn sessions and/or FALLS educational modules. Everyone completing both learning sessions and staff surveys will receive practical items (water bottles, tote bags) with the study logo.

#### Data collection from staff

Data will be collected from enrolled staff at baseline, and at three and six months following baseline. Because some nursing home staff may have low literacy or English as a second language, obtaining reliable data will require special attention; our team has experience collecting data from diverse subjects. To ensure complete and reliable data, we have chosen measures that have been used in nursing homes and are at a sixth grade reading level. Instructions for completing the questionnaires have been written to reflect Oskamp's [78] approaches to reducing response set bias due to social desirability. To ensure confidentiality, participants can place completed surveys directly in a secure drop box in the nursing home. Because surveys will be completed four times, we will change the order of the items each time to reduce the likelihood that respondents will rely on memory of previous responses.

#### Data collection from residents

A list of eligible residents who have fallen in the study periods will be obtained from the minimum data set (MDS) nurse or the falls coordinator. We will select a sample of residents via a random number generator for chart abstraction. We have obtained a waiver of Health Insurance Portability and Accountability Act of 1996 authorization and informed consent for resident chart abstraction for the falls-related process measures.

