#### Resident sample

Eligibility criteria include: > 65 years of age; sustained a fall as defined by Minimum Data Set (MDS) criteria in the study period; and remained in the facility for at least 30 days after the fall event. This sampling strategy will allow us to measure fall risk factor reduction activities completed by the nursing home staff for their highest risk residents (i.e., known fallers). Previous studies suggest a fall rate of 1.5 falls/bed-year, of which 40% are recurrent fallers [32-59]. Of the approximately 1,600 residents in the study nursing homes, we estimate a resident pool of n = 1,440 unique fallers which exceeds our needed resident sample size of 800. Lists of residents who have fallen during the study period will be generated from the nursing home MDS and incident reports. A random sample of 50 unique residents from each nursing home will be selected for chart abstraction using a random number generator. Because this is a minimal risk study in which residents are not followed prospectively, we have obtained a waiver of informed consent.

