#### Abstractor qualifications, training, and blinding

Data abstractors will hold clinical degrees and will be trained using practice charts and a manual including definitions, data locations, and detailed instructions. Instruction will be repeated until inter-rater reliability exceeds 90%. Data collectors are employed by CCME and will be blinded to the nursing home's intervention status and study hypotheses. Blinding will be assessed by asking data collectors to indicate which study group they believe the nursing home was assigned.

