### Blinding

Because of the nature of the intervention, it is not possible to mask the study assignment from the subjects or the research interventionists. However, the outcomes assessment of falls quality indicators will be completed by independent nurses employed by the state Quality Improvement Organization who will be blinded to study assignment. Success of blinding will be evaluated by asking these nurses to state which intervention they believe that the nursing home received.

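### The list of eligible fallers is supplied by unmasked nursing home staff, so the blinded chart abstraction of the Aim 1 process measures rests on an unblinded selection step

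*Protocol article*

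**What the plan says.** Three parts of the protocol article bear on how residents enter the process measures.

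- **The list.** Under 'Resident sample', "Lists of residents who have fallen during the study period will be generated from the nursing home MDS and incident reports". Under 'Data collection from residents', the list of eligible residents "will be obtained from the minimum data set (MDS) nurse or the falls coordinator".
- **The draw.** "A random sample of 50 unique residents from each nursing home will be selected for chart abstraction using a random number generator". 'Data collection from residents' makes this draw a task of the study team.
- **The blinding.** Under 'Blinding', "the outcomes assessment of falls quality indicators will be completed by independent nurses employed by the state Quality Improvement Organization who will be blinded" to assignment. The section on abstractor qualifications adds that they "will be blinded to the nursing home's intervention status and study hypotheses". For everyone else, 'Blinding' concedes that "it is not possible to mask the study assignment from the subjects or the research interventionists". The aims in 'Background' count nursing home staff among the subjects.

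Table 2 describes the FALLS Coordinator as part of the intervention. The training session opens with that role ("Researcher reviews: 1) role of FALLS Coordinator and Team members"), and the rationale column reads "Falls Team members champion fall prevention, identify area to improve, monitor changes". The coordinator also takes part in the weekly teleconferences and decides how the toolbox is disseminated. The FALLS team receives a feedback report on the home's own process and outcome measures against peer homes.

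**The concern.** The list decides who can be sampled. If the person compiling it knows the home's assignment and has a stake in the programme, the list may favour residents whose falls the team has worked up and whose charts therefore hold more of the scored indicators. Falls that were minor or never reviewed may be left off. Neither a random draw nor blinded abstraction can recover a resident who was never listed.

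The outcomes at stake are the assessment and intervention counts of H1A and H1B. The same process measures serve as mediators in H2C, so a distortion would carry into the mediation analysis.

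**Working it through.** **Which safeguards reach the list**

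| Step | Who acts | Masked? | Reaches residents left off the list? |
|---|---|---|---|
| Supply the list of eligible fallers | MDS nurse or falls coordinator | No | This is the step in question |
| Draw 50 residents by random number | Study team | Not stated | No, acts on listed names |
| Abstract charts | Quality improvement organization staff | Yes | No, acts on drawn names |
| Re-abstract 5% of charts ('Data reliability') | Second data collector | Yes | No, checks agreement on drawn charts |
| Multiple sources for falls ('Fall rate') | Data collectors | Yes | Aimed at under-reported falls, not at completeness of the list |

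The follow-up window is the six months after FALLS ends, so the follow-up list is compiled with assignment known.

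**The plan's own figures.** The required sample is 16 × 50 = 800, as stated. The pool of unique fallers reproduces as 1,600 × 1.5 × (1 − 0.40) = 1,440, also as stated (the article does not print this formula). That is 1,440 / 16 = 90 per home on the annual rate, of whom 50 / 90 = 56% are sampled.

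**Size of the possible distortion.** The documents give no indicator means by type of faller, so these inputs are assumptions: 60% of fallers are reviewed by the team, with a mean of 4 indicators, and 40% are not, with a mean of 2. All reviewed fallers are listed, and a share c of unreviewed fallers is listed.

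Mean on the list = (0.6 × 4 + 0.4 × c × 2) / (0.6 + 0.4 × c)

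- c = 100%: 3.20 / 1.00 = 3.20 (the true mean)
- c = 85%: 3.08 / 0.94 = 3.28
- c = 70%: 2.96 / 0.88 = 3.36
- c = 60%: 2.88 / 0.84 = 3.43
- c = 40%: 2.72 / 0.76 = 3.58

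Spurious difference between arms at follow-up, when baseline listing is alike in both:

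- Both arms under-list equally: ratio 1, no difference.
- 70% versus 85%: 3.364 / 3.277 = 1.027, about 2.7%.
- 60% versus 70%: 3.429 / 3.364 = 1.019, about 2%.
- 70% versus a complete list: 3.364 / 3.20 = 1.051, about 5%.
- 40% versus a complete list: 3.579 / 3.20 = 1.118, about 12%.

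**Sensitivity to the assumptions.** Suppose one arm's list omits a share m of all fallers, whose mean is r times that of listed fallers, and the other arm's list is complete. The inflation is 1 / (1 − m + m × r).

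- m = 5%, r = 0.5: 3%
- m = 10%, r = 0.5: 5%
- m = 20%, r = 0.5: 11%
- m = 20%, r = 0.25: 18%

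The comparator is the 15% difference for which 'Statistical power' claims 80% power in Aim 1.

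**The case against.** Several objections have force.

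- **The two list descriptions need not conflict.** One names the records and the other names the person who hands over the extract. A reader might infer a contradiction, or a coordinator nominating residents from memory. The text supports neither. Eligibility is mostly factual (age, a fall by the MDS definition, 30 days' stay), and the study team draws the 50. What stands is that completeness and eligibility screening are left to unmasked staff with an open choice of supplier.
- **Both arms have a coordinator.** A reader might infer that a coordinator trained for FALLS supplies the follow-up list but not the baseline list, and that this change biases the trial. The documents do not say that the supplier changes. If it did so in both arms, the effect would largely cancel, because H1A and H1B compare change between arms. Only listing that differs by arm matters.
- **Differential listing is conjecture.** It is plausible, because staff know their arm and CONNECT sets out to change team communication. Nothing in the article shows it, and its direction is not certain.
- **The coordinator is not the only issue.** The MDS nurse is unmasked too. That the lower-case falls coordinator is the Table 2 role is the natural reading but is not stated.
- **The fall rate should not be drawn in.** Table 3 builds it from several sources over occupied bed days.

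These points limit the size and scope of the problem. None of them supplies a check on the list.

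**Conclusion.** The concern holds in limited form. The article fixes a procedure in which unmasked home staff supply the sampling frame, and its blinding covers only what follows. The exposure is confined mainly to the Aim 1 process counts and their use as mediators in H2C.

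Under the assumed means, the distortion is about 2% to 3% when both arms under-list to somewhat different degrees. It is 5% to 12% only when one arm's list is selective and the other's is complete. A figure above 15% needs an extreme case, such as a fifth of all fallers missing from one arm only, with a quarter of the indicators of those listed. Stronger readings, that the result is biased or that the blinding claim is false, go beyond the text: the claim is made for outcome assessment, and arm-dependent listing is a risk, not a finding. This is a cheap improvement worth making, not a fatal flaw.

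**What to change.** Amend 'Data collection from residents' so that the blinded abstractors compile the list of eligible fallers, or verify a supplied list in full, from the MDS records and the fall or incident logs. Apply the same rule in all homes and in both six-month windows. The abstractors apply the eligibility criteria, and the study team makes the random draw as planned. Neither the falls coordinator nor the MDS nurse nominates residents or screens them for eligibility. Align 'Resident sample' with this wording.

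The cost is some extra abstractor time per home and a short addition to the abstraction manual. No new staff or data source is needed, since 'Falls data sources and abstraction timing' already has these records examined for both windows. The change does not remove differences in how unmasked staff record falls in the first place.

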#### Falls data sources and abstraction timing

Data sources include MDS, resident medical record, medication administration records, fall or incident logs, and administrative facility bed-occupancy rates. All data sources will be examined over the six months preceding study initiation and six months following the FALLS intervention. Medical records are retained in the nursing home by law for at least two years after resident discharge. The timing of abstraction is indicated in Table 3[52-62].

**Table 3 T3:** Fall measures, data sources, calculation, and time points

Concept Measured; Source	Calculation/Definition	Includes six months prior to baseline	Includes six months after FALLS ends
Demographics; Medical record	Gender, Age, and Race. Nominal	X	X

Fall rate; medical record, MDS, incident reports, census	Numerator: number of falls occurring in a 6-month period Denominator: number of occupied facility bed days	X	X

Probability of recurrent falls; as above	Proportion of residents with two or more falls occurring in a 6 month period	X	X

Fall risk reduction; medical record, MDS, incident reports	Count of documented fall risk reduction indicators defined below	X	X

a) Orthostatic Blood Pressure	Documentation of blood pressure in two positions, OR discontinuing medication, adding volume expanding medication, compression stockings	X	X

b) Sensory Impairment	Documentation of presence or absence of visual impairment, OR Intervention to change corrective devices, add assistive technology to optimize sensory input	X	X

c) Footwear	Documentation that footwear was evaluated, modified, or recommended to patient	X	X

d) Gait and Assistive Devices	Physical therapy assessment or training, change in assistive device, or participation in restorative ambulation program	X	X

e) Toileting	Documentation of scheduled toileting or a previous attempt in residents with at least intermittent urinary or bowel continence	X	X

f) Environment	Documentation of a search for environmental factors contributing to fall risk (e.g., low toilet seat, room clutter, burned out light bulb) OR a change in environment likely to reduce falls or injury risk, including repairing grab bars, changing floor surfaces, changing lighting, re-arranging furniture, using a low bed or floor mat, and alarms	X	X

g) Psychotropic Medication Reduction [53-62]	Dose reduction or discontinuation of any of the following classes of psychoactive medications within 1 month of a fall; benzodiazepines, tricyclic antidepressants, antipsychotics, propoxyphene, and selected anticholinergic agents (diphenhydramine, sedating antihistamines, immediate-release oxybutynin, skeletal muscle relaxants)	X	X

h) Calcium and Vitamin D	Prescription of at least 1,000 mg of calcium daily or 800 IU of vitamin D daily, OR equivalent dose regimens. Multivitamins containing vitamin D and combination calcium/vitamin D preparations will be added to the total daily dose calculation.	X	X

#### Abstractor qualifications, training, and blinding

Data abstractors will hold clinical degrees and will be trained using practice charts and a manual including definitions, data locations, and detailed instructions. Instruction will be repeated until inter-rater reliability exceeds 90%. Data collectors are employed by CCME and will be blinded to the nursing home's intervention status and study hypotheses. Blinding will be assessed by asking data collectors to indicate which study group they believe the nursing home was assigned.

